### Power and sample size estimation

We plan to enroll a total of 240 patients (approximately 120 per condition) in the study. Based on findings from the *REVITALIZE* pilot study and our recent RCT for adults with advanced cancer [25], we anticipate 20% missing data at 20-week FU. Accordingly, we expect data from 192 patients (*n* = 96 per group) to be available for the primary analysis of the primary endpoints for each Aim.

For Aim 1, the primary analysis will use a two-sample t-test. With a sample size of 192, the study will have 80% power to detect a significant intervention effect corresponding to Cohen’s d = 0.41 (a small-to-moderate effect size) at a two-sided alpha level of 0.05, and 94% power to detect a moderate effect size (d = 0.50). These thresholds are smaller than the effect sizes observed in the pilot trial [27], where the primary endpoint yielded approximately an effect size of d = 0.94 for the *REVITALIZE* intervention group versus EUC at follow-up, and the targeted secondary endpoints yielded effect sizes of d≥0.60. Thus, the planned sample size provides sufficient power to detect clinically meaningful effects for Aim 1.

For Aim 2, the primary analysis for chart review data will use Fisher’s exact test. With a sample size of 192, the study will have 80% power to detect an intervention effect corresponding to Cohen’s h = 0.4 (a small-to-medium effect size) at a two-sided alpha level of 0.05, and 93% power to detect a moderate effect size (h = 0.5). The longitudinal outcomes, assessed using monthly Wisepill adherence data, provide even greater statistical power than the chart review outcomes because they involve repeated continuous (rather than single binary) measurements. Accordingly, we consider the study to be adequately powered for the outcomes specified in Aim 2 [63].

For Aim 3, the power and sample size considerations are based on mediation analysis using linear regression models [64]. Let $$\:Y$$ denote the change in the primary outcome from baseline to 20 week FU, $$\:Z$$ the intervention indicator, and $$\:M$$ the mediator. We consider two models, Model 1: $$\:E\left(Y|Z\right)={\beta\:}_{0}^{*}+{\beta\:}_{1}^{*}Z$$; and Model 2: $$\:E\left(Y|Z\right)={\beta\:}_{0}+{\beta\:}_{1}Z+{\beta\:}_{2}M$$. We define $$\:({\beta\:}_{1}^{*}-{\beta\:}_{1})/{\beta\:}_{1}^{*}$$ as the proportion of treatment effect explained (PTE) and test the null hypothesis of no mediation effect (i.e., PTE = 0). Power at a two-sided 0.05 alpha for detecting mediation depends on the mediator effect size, the residual error standard deviation (SD), and the correlation between the intervention and mediator. Based on pilot data [27, 65], we conservatively estimate the SD of the residual error for the primary endpoint to be approximately 1.8. Under a correlation between condition and mediator ranging from 0.1 to 0.5, the study with *n* = 192 achieves at least 84% power to detect a mediator with the effect size of d≥0.4.

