## Methods/design

### Study design and funding

This study is a two-arm, prospective RCT that aims to randomize 240 patients with advanced ovarian cancer who are currently prescribed PARP inhibitors and report moderate to severe fatigue. Participants are individually randomized 1:1 to either *REVITALIZE* or EUC based on a randomization block sequence generated by the study biostatistician ([name]) using R statistical software [31], stratified by PARP inhibitor type and regimen (once versus twice daily and with versus without bevacizumab) and recruitment site. Patient-reported outcomes will be collected in Research Electronic Data Capture (REDCap) [32], a HIPAA-approved, secure, web-based tool, at five timepoints: baseline (pre-intervention), mid-intervention (8 weeks after baseline), post-intervention (13 weeks after baseline), and 20- and 28-week follow-ups (FU). The 20-week FU serves as the main endpoint, and the 28-week FU serves to assess maintenance or change in effects over time. Adherence outcomes will be assessed via Wisepill, a wireless adherence tracking device [33] and medical chart review.

The study was pre-registered with identifier NCT06710548 on Clinicaltrials.gov on November 29, 2024, before enrolling the first patient (https://clinicaltrials.gov/study/NCT06710548). Dana-Farber Cancer Institute serves as the single IRB overseeing the study and informed consent is obtained from all individuals prior to study enrollment.

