### Study ethics and integrity

The Dana-Farber Cancer Institute (DFCI) serves as the single IRB for the study. The internal Data Safety and Monitoring Board at DFCI provides additional oversight for data quality, participant safety, and assessment of potential harms. Verbal informed consent is obtained from all study participants, preceded by a verbal discussion of the consent form in person or by phone with a trained study RA to facilitate full understanding prior to signing. At the beginning of the baseline survey in REDCap, participants sign a HIPAA release appropriate to their site to grant permission for the study team to confirm medical eligibility and treatment information in their medical records. Following completion of the baseline survey, the participant is then sent a wireless electronic pillbox (Wisepill) and completes an orientation with a trained study RA, so the participant understands how to use the device. Study coordinators randomize participants using a sequence created by the study biostatistician. The sequence is uploaded into REDCap using the embedded randomization function wherein the sequence is hidden from the study team to reduce potential bias and once assigned cannot be altered. Data confidentiality is ensured by the collection and storage of patient-reported outcome data in REDCap, a HIPAA-compliant system. To reduce potential bias in outcome assessment, REDCap survey links are sent to participants directly. Participant retention and timely data collection are promoted by compensating participants for their time in completing the online assessments. All research team members complete relevant Collaborative Institutional Training Initiative (CITI) training and all university-affiliated members report an annual Disclosure of External Professional Activities (DEPA).

Each study recruitment site completes a site initiation visit prior to onboarding in which study details are presented and discussed. The MPIs have a standing weekly to biweekly meeting and the study coordinators have a standing weekly to biweekly meeting with the MPIs to ensure timely study communication, coordination, and troubleshooting across the administrative sites. Protocol modifications will be submitted for approval to the DFCI IRB and once approved, communicated to the study coordinators at this standing meeting. The senior leadership team (e.g., study Co-Is) meets regularly to review recruitment rates, protocol changes, and study-related updates.

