#### PARP inhibitor adherence assessment (Aim 2)

To assess monthly PARP inhibitor adherence and non-persistence, we will use Wisepill, a simple wireless electronic pillbox monitoring device (4.3”x1.8”x.5”) that sends real-time data to a protected online server when opened. This enables quick identification of any device issues and transmitting full data even if devices are not returned. Wisepill is highly reliable, acceptable, and easy to use [52–55]. It shows similar reliability as MEMS caps [56], greater accuracy than real-time reporting [57], pill counts or self-report [35, 56, 58], and direct association with biologically-measured adherence markers [57]. We used Wisepill to assess anti-cancer medication adherence in prior work [35, 52, 59]. This work established successful procedures for the remote delivery, instructions, and return of Wisepill monitors using post mail that we use in the current study. Study RA’s also complete a phone orientation with each participant to instruct them on how to use the Wisepill and confirm that it is working properly.

Wisepill adherence tracking device data will compute monthly PARP inhibitor adherence as the percent of days per 30-day month that the tracking device is opened once for each dose prescribed that day, divided by 30, using recommended methods for Wisepill data preparation and analysis [53]. PARP inhibitors that are taken once daily will require one Wisepill opening to be considered adherent on that day, whereas PARP inhibitors taken once in AM and once in PM will require two Wisepill openings at separate times to be considered adherent on that day. (As noted above, we stratify by PARP inhibitor regimen to take into account dosing schedules across study arms).

Wisepill-assessed monthly adherence will serve as the main adherence outcome. Wisepill, along with medical chart review, will also assess PARP inhibitor non-persistence, measured as stopping the PARP and not restarting through study end. Finally, medical chart review will be used to evaluate PARP inhibitor dose reductions and interruptions, the latter defined as breaks in PARP inhibitor use that reflect stopping and starting again during the study rather than stopping through study end, and disease progression events.

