### Data analytic approach

The statistical analysis will be conducted according to the intention-to-treat principle, with all randomized participants included in the primary analyses. Descriptive statistics will be used to evaluate baseline and follow-up outcome measures, including assessment of distributions, potential outliers, and patterns of missing data. For continuous outcomes, we will summarize mean changes from baseline with corresponding 95% confidence intervals (CIs) at each follow-up time point for both groups (Enhanced Usual Care vs. *REVITALIZE*). For binary outcomes (e.g., presence of PARP inhibitor dose delays, interruptions, or discontinuation), we will estimate proportions with corresponding 95% CIs. If clinically meaningful imbalances are observed between groups, adjusted analyses using regression or stratified models will be performed.

For Aim 1, the primary analysis of change in fatigue interference at week 20 will tested using a a two-sample t test (without covariate adjustment). As a secondary analysis, linear regression (ANCOVA) of the outcome on the intervention indicator, adjusting for the baseline value of the outcome and prespecified baseline variables (race/ethnicity, education, age, and income) will be used. If any baseline variable shows imbalance (standardized mean difference > 0.10), it will be retained in the regression model; otherwise only the baseline value of the outcome will be included alongside the variable for condition. Longitudinal mixed-effects models will be conducted as additional secondary and sensitivity analyses. Aim 2 adherence outcomes will be assessed using mixed-effects models for Wisepill data and logistic regression for binary adherence indicators. Aim 3 will evaluate whether the conditions differ on change over time in the hypothesized process variables for *REVITALIZE—* acceptance and values alignment. In addition, we will test mediation of intervention effects on fatigue interference through acceptance and values alignment using the linear regression mediation framework outlined below as well as the multiple mediation framework of Preacher and Hayes [62], with sensitivity analyses using structural equation models.

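### Aim 2 chart-review outcomes are powered on 192 patients using a week-20 attrition figure that does not apply to medical records, and the analysis set should be stated as all randomized patients with an accessible chart

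*Protocol article*

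**What the plan says.** All references are to the Protocol article.

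- **Power and sample size estimation** sets enrolment: "We plan to enroll a total of 240 patients (approximately 120 per condition) in the study". It then says "we anticipate 20% missing data at 20-week FU" and expects 192 patients (96 per group) "to be available for the primary analysis of the primary endpoints for each Aim".
- The same section names the test: "For Aim 2, the primary analysis for chart review data will use Fisher’s exact test". At a sample size of 192 and two-sided alpha 0.05 it claims 80% power for Cohen's h = 0.4 and 93% for h = 0.5.
- **PARP inhibitor adherence assessment (Aim 2)** gives the data source: "medical chart review will be used to evaluate PARP inhibitor dose reductions and interruptions". Progression events also come from the chart. Non-persistence is assessed by Wisepill together with the chart, through study end.
- **Study ethics and integrity** describes a release, signed at the start of the baseline survey, in which participants "grant permission for the study team to confirm medical eligibility and treatment information in their medical records". **Study timeline** places that survey before randomization.
- **Data analytic approach** commits to intention-to-treat, "with all randomized participants included in the primary analyses". Its missing-data paragraph also speaks of a complete-case analysis.
- **Measures** lets patients who leave the intervention or progress keep completing assessments. It does not mention chart abstraction.

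**The concern.** The 20% figure describes data missing at a follow-up visit. It suits outcomes that need the patient to do something: return a survey or open a pillbox. It has no evident bearing on dose reductions, interruptions or progression read from a chart to which access was granted at baseline, and the article gives no reason why one chart in five would be unreadable. The text therefore leaves two readings of the Aim 2 chart-review analysis set: everyone randomized, or those with week-20 data.

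Two things depend on which reading is used:

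- **Power.** Up to 48 patients' chart outcomes would be given up.
- **Selection.** If patients who stop the PARP inhibitor or progress also tend to leave the study, limiting the analysis to those who remain would select on the outcome. Event rates would be understated, and the arm comparison could be distorted.

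**Working it through.** **Inputs.** From Power and sample size estimation: N = 240, 20% missing, h = 0.4 and 0.5, two-sided alpha 0.05, Fisher's exact test. From Study design and funding: "Participants are individually randomized 1:1 to either" REVITALIZE or control. The article gives no event rates for the chart outcomes, so control rates of 10% to 60% are assumed.

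**1. Reproduce the plan's figures.** 240 × (1 − 0.20) = 192, or 96 per arm. Arcsine approximation: power = Φ(h·√(n/2) − 1.96), with n per arm.

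- n = 96, h = 0.4: Φ(0.4 × 6.928 − 1.96) = Φ(0.811) = 79.1% (stated 80%)
- n = 96, h = 0.5: Φ(0.5 × 6.928 − 1.96) = Φ(1.504) = 93.4% (stated 93%)

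The stated values match this approximation.

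**2. Same formula with all charts (n = 120).**

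- h = 0.4: Φ(0.4 × 7.746 − 1.96) = 87.2%
- h = 0.5: 97.2%
- The h detectable with 80% power, (1.96 + 0.842)/√(n/2), falls from 0.404 to 0.362.

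**3. The named test.** Two-sided Fisher power at h = 0.4 by exact enumeration. The second rate is p2 = sin²(arcsin√p1 − h/2). The 114-per-arm column represents 5% of charts unavailable (120 × 0.95).

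| Assumed control rate p1 | p2 | 96 per arm | 114 per arm | 120 per arm |
|---|---|---|---|---|
| 10% | 1.5% | 65% | 76% | 77% |
| 20% | 6.8% | 72% | 80% | 82% |
| 30% | 13.7% | 74% | 82% | 84% |
| 40% | 21.7% | 75% | 82% | 84% |
| 50% | 30.5% | 74% | 82% | 85% |
| 60% | 40.1% | 75% | 83% | 83% |

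**4. Separate the two effects.** At 96 per arm, moving from the arcsine figure (79.1%) to Fisher's test costs about 4 to 7 points for control rates of 20-60% (79.1 − 75.0 = 4.1; 79.1 − 72.4 = 6.7). That loss has nothing to do with attrition. Going from 96 to 120 per arm under Fisher's test gains about 8 to 11 points over the same rates (60%: 83.4 − 75.0 = 8.4; 50%: 84.9 − 74.2 = 10.7).

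**5. Illustration of selective loss (all rates assumed).** Take true stop rates of 40% v 22%, 20% missing overall, and 40% missing among stoppers. The mean stop rate is 31%, so missingness among non-stoppers is (0.20 − 0.40 × 0.31)/0.69 = 0.11. Observed rates are:

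- control: 0.40 × 0.60 / (0.40 × 0.60 + 0.60 × 0.89) = 31%
- intervention: 0.22 × 0.60 / (0.22 × 0.60 + 0.78 × 0.89) = 16%

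h falls from 0.39 to 0.36. Fisher power is 64% with 96 per arm, against 83% with all 120 per arm. This shows what could happen; it does not estimate what will.

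**The case against.** The strongest reply is that 192 is a forecast used for power, not a definition of who is analysed. The analysis set is in Data analytic approach, and it is everyone randomized. Powering on fewer patients than are randomized is ordinary and conservative, and post-dropout chart abstraction is the kind of detail an article leaves to the full protocol.

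Much of this stands, and it rules out several stronger readings:

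- **That 48 patients are dropped from the chart analysis.** A reader might infer this from the 192, but no text orders it. The mention of a complete-case analysis makes it possible, no more.
- **That the missing patients are those who stopped the drug.** This is plausible but undocumented. Measures lets patients who leave the intervention or progress continue assessments.
- **That all 240 charts will be readable.** The baseline release supports access, but the article does not say what happens after withdrawal of consent or transfer of care. 240 is an upper bound.
- **That every Aim 2 outcome is free of device data.** Non-persistence uses Wisepill as well as the chart, and monthly Wisepill adherence is the main adherence outcome. For that outcome an allowance for missing data is reasonable.
- **That the attrition figure explains the gap between 80% and 72-75%.** It does not; the arcsine approximation does.

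What the reply does not answer is that the article explicitly powers the chart-review test at 192, gives no reason for 20% of charts to be missing, and states a power that the named test does not reach at that size. Calling 192 conservative fails under Fisher's test, because the stated 80% is missed at every control rate tried.

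**Conclusion.** The point holds as a matter of an ill-fitting planning number, an ambiguous analysis set and a misstated power. It does not hold as a finding that outcomes are being discarded or that bias is built in.

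Under Fisher's test at h = 0.4, planning on 192 gives about 65-75% power over assumed control rates of 10-60%, against the stated 80%. Reading every chart gives 82-85% for rates of 20-60%, and losing 5% of charts still gives 80-83%. At a 10% control rate the target is missed in either case (77% and 76%). These figures rest on the assumed control rates. The selection risk rests on two further conditions: that the analysis set follows the 192, and that stopping, progression and study exit cluster.

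**What to change.** 1. In Measures and in PARP inhibitor adherence assessment (Aim 2), state that chart abstraction of PARP inhibitor stops, restarts, dose changes and progression continues through study end for all randomized participants, whatever their survey, session or Wisepill status, unless authorization is withdrawn.
2. In Data analytic approach, state that chart-review outcomes are analysed in all randomized participants with an accessible chart (up to 240), and say how non-persistence is determined when Wisepill data stop but the chart is available.
3. In Power and sample size estimation, keep 192 only for outcomes that need participant input. Restate the chart-review power with Fisher's exact test for the number of charts expected, with the assumed control rates shown.

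The cost is wording and abstraction of up to about 48 more charts (240 − 192). No new patients or study procedures are needed.

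### The Aim 2 power figures (80% and 93%) are those of a large-sample test; the Fisher's exact test named beside them gives about 71–75% and 90–91.5%, and the analysis section names logistic regression instead

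*Protocol article*

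**What the plan says.** The power section of the protocol article starts from enrolment ("We plan to enroll a total of 240 patients (approximately 120 per condition) in the study"), assumes a loss ("we anticipate 20% missing data at 20-week FU"), and concludes that "we expect data from 192 patients", 96 per group, for the primary analysis of each Aim.

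For Aim 2 it states that "the primary analysis for chart review data will use Fisher’s exact test". It then says "the study will have 80% power to detect an intervention effect corresponding to" Cohen's h = 0.4 at two-sided 0.05, and 93% power at h = 0.5. No event rates are given.

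For monthly Wisepill adherence, which the Measures section makes the main adherence outcome, it says that these longitudinal outcomes "provide even greater statistical power than the chart review outcomes because they involve repeated continuous (rather than single binary) measurements". From this it concludes that Aim 2 is adequately powered.

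The Data analytic approach section assigns mixed-effects models to the Wisepill data and "logistic regression for binary adherence indicators". It does not mention Fisher's exact test.

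**The concern.** A power statement belongs to a particular test. The ordinary Fisher's exact test is conservative: with discrete data its actual type I error lies below 0.05, which costs power compared with a large-sample test. Power computed from Cohen's h by the usual normal formula therefore does not carry over to it.

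Two things are at stake. The adequacy claim for the chart-review outcomes rests on figures that the named test does not deliver. In addition, the two sections point to different methods for the same outcomes. Near the 0.05 boundary the methods can disagree, so the one that decides should be fixed beforehand.

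The claim for Wisepill adherence is inferred from the chart-review power and the type of data. Power depends on that outcome's own effect size, variability and within-person correlation, and none of these is stated.

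**Working it through.** **Inputs from the protocol article.** 96 per arm (240 × 0.8 = 192, split 1:1), two-sided alpha 0.05, h = 0.4 and h = 0.5.

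**Assumed input.** The lower of the two arms' event rates, p1, scanned from 5% to 80%, with rarer rates shown separately.

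**Step 1: reproduce the stated figures.** The arcsine normal approximation is power = Φ(h × √(n/2) − 1.96), with n = 96 and √48 = 6.928.
- h = 0.4: 0.4 × 6.928 − 1.960 = 0.811, so power is 79.1% (stated: 80%).
- h = 0.5: 0.5 × 6.928 − 1.960 = 1.504, so power is 93.4% (stated: 93%).
- h for exactly 80%: (1.960 + 0.842) / 6.928 = 0.404, which rounds to 0.4.

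Both stated figures are reproduced to within rounding of h.

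**Step 2: power of the test that is named.** The higher rate is p2 = sin²(arcsin√p1 + h/2). For example, with p1 = 0.20 and h = 0.4, arcsin√0.20 = 0.4636 and sin²(0.6636) = 0.379. Power is the sum of the binomial probabilities of all 97 × 97 outcomes at which the two-sided Fisher p-value is at most 0.05.

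| p1 | p2 (h = 0.4) | Fisher power | p2 (h = 0.5) | Fisher power |
|---|---|---|---|---|
| 1% | 8.7% | 62.2% | 11.8% | 86.3% |
| 3% | 13.4% | 69.7% | 16.9% | 89.1% |
| 5% | 17.0% | 71.1% | 21.0% | 89.9% |
| 10% | 24.8% | 73.6% | 29.3% | 91.0% |
| 20% | 37.9% | 74.5% | 42.8% | 91.3% |
| 30% | 49.4% | 74.2% | 54.4% | 91.2% |
| 40% | 59.9% | 75.0% | 64.7% | 91.5% |
| 50% | 69.5% | 74.2% | 74.0% | 91.1% |
| 80% | 93.2% | 72.4% | 95.5% | 89.7% |

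Over the whole scan, in 1-point steps, Fisher's power peaks at 75.0% for h = 0.4 and at 91.5% for h = 0.5. No choice of event rate brings it to 80% or 93%.

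**Step 3: which tests fit the stated figures.** The same enumeration for the pooled chi-square test and for the likelihood-ratio test of an unadjusted logistic regression, at the tabulated rates from 5% to 50%, gives 78.6–79.5% at h = 0.4 and 93.2–93.5% at h = 0.5. Any of the three large-sample tests therefore explains both figures.

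**Step 4: what Fisher could support.** With 96 per arm, 80% power needs h of about 0.43–0.44. At h = 0.4, 80% power needs about 110–112 analysable patients per arm (p1 from 10% to 40%).

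**The case against.** **Rounding.** If h = 0.4 were a rounded 0.43, Fisher's test would reach 80%. But the 93% at h = 0.5 lies above Fisher's maximum of 91.5%, while the large-sample formula accounts for both figures.

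**The figures may be right and the label wrong.** This stands. About 79% and 93% also fit an unadjusted logistic regression, the method named in the analysis section. The documents do not show which calculation was run, so the arcsine formula cannot be singled out as the source.

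**Two competing primary tests.** A reader might infer this, but only the power section uses the word primary, for Fisher. Logistic regression could be a further analysis, as ANCOVA follows the t-test in Aim 1. For Aim 1, though, the analysis section states that order; for Aim 2 it gives none and omits Fisher.

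**The 192.** A reader might call this wrong for chart review, which needs no completed survey. The documents do not say that charts will be complete for all 240, and they apply the loss to every Aim, so 192 is cautious planning. With all 120 per arm, Fisher would have 81.6–84.9% at h = 0.4 (p1 from 5% to 50%), but the stated power is not based on that number.

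**Wisepill.** A reader might infer that this outcome is underpowered. The documents do not show that. The variance of a mean of six monthly values relative to one is (1 + 5ρ)/6, with six values and ρ both assumed: 0.83 at ρ = 0.8 and 0.58 at ρ = 0.5, so the gain from repetition varies widely. Nor is a detailed Wisepill calculation required in an article. What fails is only the stated inference.

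**Conclusion.** The point holds for Aim 2. At h = 0.4 with 96 per arm, Fisher's exact test has about 71–75% power rather than 80%, a shortfall of 5 to 9 points. At h = 0.5 it has about 90–91.5% rather than 93%, a shortfall of roughly 2 to 3 points. These ranges assume lower-arm event rates of 5–80%; rarer events do worse (62.2% at h = 0.4 for 1% versus 8.7%). The stated figures belong to a large-sample test, and the two sections do not name the same method.

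The reasoning that repeated, continuous measurement gives Wisepill adherence more power than the chart-review outcomes does not follow, because it is a different outcome with its own effect size. This does not show that its power is low.

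A reader might go further and infer that the trial as a whole is underpowered. The documents do not support that: the primary fatigue outcome and the enrolment target do not depend on these figures.

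**What to change.** Name one primary test for the chart-review outcomes in both Power and sample size estimation and Data analytic approach. State the power of that test with the event rates assumed.

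- If Fisher's exact test is kept: with 192 patients, state about 71–75% at h = 0.4 and about 90–91% at h = 0.5, or give a detectable h of about 0.43–0.44 for 80% power. Describe logistic regression as a further analysis.
- If unadjusted logistic regression (likelihood-ratio test) or the chi-square test is made primary: about 79% and 93% can stand, and the reference to Fisher should go.

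Delete or reword the sentence on Wisepill power. If an adequacy claim is kept for that outcome, base it on its own assumed SD, within-person correlation and detectable difference.

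The cost is rewording and a recalculated figure. No additional patients are needed.

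### The Aim 3 claim of at least 84% power to reject PTE = 0 fails at the low end of the stated condition-mediator correlations: about 28% at r = 0.1, with 84% possible only from r of about 0.21

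*Protocol article*

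**What the plan says.** The Aim 3 paragraph of Power and sample size estimation sets up two linear models for Y, the change in the primary outcome to week 20. Model 1 contains the intervention indicator Z alone, with coefficient beta1*. Model 2 contains Z (beta1) and the mediator M (beta2). It defines PTE as (beta1* - beta1)/beta1* and says that the trial will "test the null hypothesis of no mediation effect (i.e., PTE = 0"). The test is two-sided at 0.05: "Power at a two-sided 0.05 alpha for detecting mediation depends on the mediator effect size", the residual SD and the correlation between condition and mediator. On the residual SD: "we conservatively estimate the SD of the residual error for the primary endpoint to be approximately 1.8".

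The claim follows: "Under a correlation between condition and mediator ranging from 0.1 to 0.5", n = 192 "achieves at least 84% power to detect a mediator with the effect size of" d of at least 0.4. The article does not say what d is scaled to.

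The 192 comes from the start of the same section: "We plan to enroll a total of 240 patients (approximately 120 per condition) in the study", "we anticipate 20% missing data at 20-week FU", and hence "we expect data from 192 patients" for the primary analysis of each aim.

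**The concern.** A single power floor is given for the whole range of r, down to 0.1. But r measures how far the intervention moves the mediator, and mediation requires that movement. At r = 0.1 the movement is small, and 192 patients cannot detect it reliably. A power near 84% there does not fit the stated null.

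Mechanism is one of the trial's three aims. Readers who rely on the stated floor would regard the mediation test as well powered even for a weakly moved mediator, where most true indirect effects would be missed.

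**Working it through.** **Inputs.** n = 192, two-sided alpha 0.05, r from 0.1 to 0.5, d = 0.4 and residual SD 1.8 (all Power and sample size estimation); 1:1 allocation (Study design and funding).

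**Step 1: what PTE = 0 means.** Let a be the effect of Z on M. In these two linear models, beta1* - beta1 = a x beta2. With beta1* not zero, PTE = 0 if a = 0 or beta2 = 0. Rejecting the null needs evidence on both paths, so power is capped at about the power to detect a.

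**Step 2: the cap.** The t test of a = 0 has 190 degrees of freedom and noncentrality r x sqrt(n) / sqrt(1 - r^2). At r = 0.1 this is 0.1 x 13.856 / 0.995 = 1.39, well short of the critical value of about 1.97. The between-arm difference on M, in within-arm SDs, is 2r / sqrt(1 - r^2).

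| r | Difference on M (SD) | Power for a, n = 192 |
|---|---|---|
| 0.10 | 0.20 | 28.3% |
| 0.15 | 0.30 | 55.2% |
| 0.20 | 0.41 | 80.3% |
| 0.21 | 0.43 | 84.2% |
| 0.30 | 0.63 | 99.1% |

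A Fisher z approximation gives 28.1% at r = 0.1. The cap does not involve beta2, so it does not depend on the scale of d.

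**Step 3: the protocol's own Aim 1 figure.** Aim 1 states 80% power at d = 0.41 with n = 192, and the t test reproduces this (80.7%). The mediator comparison has the same design, and r = 0.2 corresponds to d of about 0.41 with 80.3% power. At r = 0.1 the difference is d of about 0.20, half of what the article says is needed for 80%.

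**Step 4: trying to reproduce 84%.** The nearest match is a test of beta2 alone, with r entering only through variance inflation. If 0.4 is taken as raw points per SD of M (an assumption), the noncentrality is (0.4/1.8) x sqrt(n(1 - r^2)). At n = 192 this gives 86.2%, 85.1%, 83.2%, 80.2% and 75.6% at r = 0.1, 0.2, 0.3, 0.4 and 0.5. If 0.4 is standardised, power is at least 99.8% throughout. Neither gives a floor of 84% over the range, and neither is a test of PTE = 0.

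**Step 5: joint-significance power at n = 192** (power for a times power for beta2).

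| r | d standardised | 0.4 raw per SD of M, SD 1.8 |
|---|---|---|
| 0.1 | 28% | 24% |
| 0.2 | 80% | 68% |
| 0.3 | 99% | 82.5% |
| 0.4 | above 99% | 80% |
| 0.5 | above 99% | 76% |

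For example, raw scaling at r = 0.1 gives 0.283 x 0.862 = 0.244.

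**Step 6: simulation** (800 runs per setting, three strengths of the mediator-outcome link). At r = 0.1, joint significance gave 24-29%, Sobel 11-29%, percentile bootstrap 24-31% and bias-corrected bootstrap 32-33%. With r = 0 the bias-corrected bootstrap rejected in 5-8% of runs, so its extra power comes with some inflation of type I error.

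**The case against.** The best defence is that the 84% describes the mediator-outcome coefficient. On the raw scaling that test does have about 86% power at r = 0.1. But the paragraph names PTE = 0 as the null, and with r = 0, where PTE is truly zero, the beta2 test rejected in 86-100% of simulated trials. The defence may explain the number; it does not make it power for mediation.

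Four limits on the point stand. First, the cap applies to tests that hold 5%; the bias-corrected bootstrap goes somewhat above it. Second, the shortfall common to every scaling of d is confined to r below about 0.21. Third, the method behind the power calculation is cited rather than described, so the scale of d cannot be settled from the article. Fourth, nothing says that Aim 3 set the sample size, and Aim 1 is unaffected.

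Three stronger readings are tempting, and the article supports none of them:

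- *That a process the intervention does not change could be declared a mechanism.* Data analytic approach compares the arms on change in the process variables and adds a multiple-mediation framework with structural equation models as sensitivity analyses. No test of beta2 alone is planned. The error shown is in the power statement, not in the analysis.
- *That the enrolled 240 was used in place of 192.* On the raw scaling, 240 patients give 84.4% for beta2 at r = 0.5, which is suggestive. It rests on an assumed scale for d; on the standardised scale nothing points to 240.
- *That the models wrongly omit baseline values.* Y is already a change from baseline, M may be one too, and covariates for this analysis can be left to the statistical analysis plan.

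**Conclusion.** The Aim 3 power statement is wrong as written. For the null it names, power at n = 192 and r = 0.1 is about 28% at best with a test holding 5% (32-33% with a mildly anti-conservative bootstrap), against a stated floor of 84%. At r = 0.15 the cap is 55% and at r = 0.2 it is 80%. These figures use only n, alpha and r from the article and the usual normal-error linear models.

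Above r of about 0.21 the answer depends on the undefined d. If it is standardised, the claim holds from there to 0.5. If it is raw points per SD of M with residual SD 1.8, joint-significance power stays below 84% at every r. On that scaling only the bias-corrected bootstrap passed 84% (85% in 800 runs at r = 0.3), with the type I inflation already noted.

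**What to change.** In the Aim 3 paragraph:

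1. Define the scale of d for the mediator effect.
2. Restate power for the test of the indirect effect that will be used, tabulated by r at n = 192.
3. Either limit the stated range to the r values at which the quoted power holds, or keep 0.1 to 0.5 and report the lower power at the low end.
4. Give the smallest r with 80% power, which is about 0.20 at best.

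The cost is a short recalculation, some rewording and a less favourable stated power. The design, sample size and data collection do not change.
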